### Coach workshops

Two, three hour, workshops involving a mixture of theory and practical content, designed by the Principle Investigator and lead investigator from each of the sites (site lead) will be delivered by each site lead, in- country, to four facilitators. The format of the coach learning session will be: (i) the nature of children’s movement development, (ii) rationale, structure and purpose of MOGBA, (iii) intervention programme of activities, (iv) changing the challenge, (v) differentiating opportunities (vi) assessing and recording movement competence and (vii) using assessment to guide teaching and improve movement competence.

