## Abstract

There is a positive relationship between children’s movement competence and physical activity, with a further relationship established between physical activity and childhood obesity. The Movement Oriented Games Based Assessment (MOGBA) is a delivery and assessment intervention designed to improve children’s complex movement skills, based on principles of motor development and assessment theories. MOGBA aims to improve children’s movement competence, physical fitness and self-perceptions (physical and game) and increase children’s moderate-to-vigorous physical activity (MVPA). MOGBA is to be used in the ‘Made to Play’ initiative, involving 105 sports and activity programs across 21 countries, involving over 25 million children. A multi-site cluster randomized controlled trial will take place across three global sites (UK, Ireland and Australia). Each site will recruit eight primary schools (four experiment, four control) with each school providing two separate classes of children from age ranges 8–12 years (Site n = ~300, total n = 904). After baseline assessments, schools will be randomly allocated to an experimental or wait-list control group. Following two half-day workshops, trained facilitators will deliver the MOGBA intervention for 9 weeks. The main intervention components include delivery of 14 games-based activities with associated assessments of children’s movement and differentiation to meet children’s needs by manipulating space, effort and relationships. The primary outcome of the trial is to improve children’s’ movement competence (The Dragon Challenge), with secondary outcomes of improving children’s’ in-activity and leisure-time MVPA (5-day accelerometer), physical fitness (standing long jump and push ups) and self-perceptions (physical and game). Data will be analysed using multilevel modelling approaches. The MOGBA intervention has been designed to improve children’s movement competence and scalable interventions based on MOGBA could be applied across programs within the Made to Play initiative, globally. The trial is registered at the Australia New Zealand Clinical Trial Registry (ACTRN12619001320145p, 27 Sep 2019).

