### Trial design

A cluster randomized control trial will be used to assess the effectiveness of MOGBA in a school setting, as this is perceived to be an ideal setting for the promotion of movement competence and PA [22]. Another potential option available was to establish the trial within MTP programs, as clusters. It was felt that, due to the eclectic and disparate nature of these programs, controlling and accounting for the variability both within intervention and control groups would be more problematic than a school setting. It is intended to use the findings of this trial to inform the scalability of MOGBA across MTP programs.

Through the trial we aim to examine whether MOGBA (a) improves children’s movement competence; (b) increases Moderate to Vigorous Physical Activity (MVPA during PE lessons, (c) increases MVPA time in school (d), improves physical fitness, (e) improves self-perceptions of game and physical competence. We hypothesize that children in the MOGBA intervention, compared to those in the control group, will display more favorable changes in movement competence, physical activity, physical fitness, physical self-perceptions and game perceptions.

The 9-week intervention will be delivered during the school day and target children in the school years containing the age ranges 8/9, 9/10, 10/11, 11/12 years. Baseline measures, including all primary and secondary outcomes, will be taken prior to the commencement of the intervention, which will be staggered across the sites to prevent clashes with key educational milestones within the respective countries. This is a deviation from the original study protocol in which there was originally 4 sites, including the USA, which was subsequently reduced to 3 sites as a result of Covid-19 restrictions on accessing schools. After baseline measures are taken, schools will be randomly allocated into either an intervention or wait-list control group. Schools allocated to the experimental group will be assigned a facilitator to deliver the 14 MOGBA activities across a 9-week period.

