### Sample size calculation

A sample size calculation was completed to estimate the number of schools needed for the trial. Sampling for a two-group clustered RCT is developed around data from previous clustered trials assessing game skill (e.g., support, decision-making and defence) and fundamental movement skill (e.g., throw, kick, under-arm throw and catch) development [23, 24]. The lowest effects in these trails were observed for the fundamental movement skill of catch (effect *d* = 0.4), and the game skill of decision making (*d* = 0.4).

Without accounting for clustering among schools (schools being alike and reducing the power of data), approximately 156 students are required to detect an effect of d = 0.4 at 80% power with alpha 0.05. To adjust for clustering, the following correction factor is applied (1+ (m– 1) x ICC) [25], where m = students per school and ICC = the intra-class correlation coefficient (between school variance / between school variance + within school variance). Assumptions are based on clustering at the school level (one class recruited per school, with ~25 students per class), and a conservative ICC of 0.20 based on data from a school based intervention [22], resulting in a correction factor of 5.8. The resulting student sample is ~904 students at 36 schools (18 intervention, 18 control).

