### Setting and participants

To align with the typical motor development phase associated with CMS, recruitment of participants will be targeted at children 8–12 years, spread across 4 school years/grades. As this age range straddles two levels of schooling (primary/elementary, secondary/middle) 6 schools from each level at each site will be invited to the trial. Existing university networks will be used to recruit schools and if more than the required number of schools replies positively, schools will be stratified into age groupings prior to random selection (coin toss) of inclusion into the study. Recruitment will result in 3 sites each containing 12 schools (6 experiment, 6 control) evenly distributed across primary/elementary, secondary/middle schools yielding approximately 300 students at each site and a total of ~904 students for the trial. Representatives of each school will be invited to an information event to support their decision-making in becoming involved.

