### Intervention

MOGBA is presented as a series of 14 resource cards with the front of the card illustrating the game as well as sections describing ’what you need’ (equipment), ’set up like this’, ’keep it safe’ and ’change the game’. On the reverse of the card, there is an assessment framework that illustrates the movement being assessed and provides criteria for the practitioner to use to score the child’s performance using two constructs. The assessment has two focal aspects most closely related to the movement being assessed (i.e. two aspecsts from: head, arms, legs or body) with associated criteria, alongside which the numerical values are placed following a child’s assessment. Given the complex nature of the assessment and projected groups size (20–25 children), a subset of children will be selected for assessment during each activity.

The resource also contains an ’introductory section’ that explains the nature of children’s movement development and the purpose of MOGBA, as well as a ’change the challenge’ section. ’Change the challenge’ provides guidance for practitioners on how to differentiate the activity to meet the diverse needs of children in relation to Goodway, Osmun & Gallahue’s [1] notion of Space, Effort and Relationships.

Facilitators recruited by each site will deliver the 14 MOGBA activities in schools over a 9-week period, following two three-hour facilitator development workshops. Facilitators are affiliated to the University and have considerable experience in Physical Education and/or coaching settings. At each site, all 14 MOGBA activities, ranging in categories (Stability (S), Object Control (OC) and Locomotion (L)) and complexity of movement (across three phases) will be delivered, with two sessions each week lasting between 45–60 minutes per session. One MOGBA activity, as presented on the front of the activity resource card and use of the associated assessment protocol will last the duration of the session. An extra four sessions have been accounted for within the intervention period to cater for typical disruptions to timetables. Fig 1 provides an example of the ‘Play it’ side of a MOGBA activity resource card.

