### Statistical analyses

This trial aims to examine whether MOGBA (a) improves children’s movement competence (Dragon Challenge); (b) increases MVPA during PE lessons (acceleromters), (c) reduces sedentary time both in school and outside of school (accelerometers) (d), improves physical fitness (plank and standing long jump), (e) improves self-perceptions of game and physical competence (Game Play Perception Profile). We hypothesize that children in the MOGBA intervention, compared to those in the control group, will display more favorable changes in these variables identified above.

Statistical analyses of the primary and secondary outcomes will be conducted with linear mixed models using IBM PASW Statistics 25 (SPSS Inc. Chicago, IL) software. Impacts are estimated using an intention-to-treat (ITT) approach, with alpha levels set at p < 0.05. Linear mixed models will be fitted to compare continuous outcomes. Group, time, and group-by-time interaction will be assessed as fixed effects within the model, with covariates of gender and year level also included as fixed effects. The school a student belongs to and the research site will be included as a random intercepts within the model to account for the multi-level nature of the data, and subject (student ID) will be included as a random intercept to model repeated measures at the individual level. Differences of means and 95% confidence intervals (CIs) will be determined using the linear mixed models. If the variables used for secondary outcomes (questionnaires) fail tests of multivariate normality, non-parametric methods will be utilised, or the variables for use in the linear models will be an individual’s factor score from a confirmatory factor analysis of the scales with the appropriate estimator chosen given the non/normal nature of the data.

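### On the 36-school design, four facilitators per site cannot each take one of six intervention schools, and the planned model has no term for a facilitator effect shared between schools

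*Protocol article*

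**What the plan says.** All places are in the Protocol article.

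- Coach workshops: training "will be delivered by each site lead, in- country, to four facilitators". No other trained deliverers are described.
- Intervention: "Facilitators recruited by each site will deliver the 14 MOGBA activities in schools over a 9-week period".
- Trial design: "Schools allocated to the experimental group will be assigned a facilitator to deliver the 14 MOGBA activities across a 9-week period". One-to-one assignment is not stated.
- Setting and participants: "Recruitment will result in 3 sites each containing 12 schools (6 experiment, 6 control").
- Sample size calculation: "The resulting student sample is ~904 students at 36 schools (18 intervention, 18 control"). Clustering is allowed for at school level only, with ICC 0.20 and one class of about 25 per school.
- Abstract: "Each site will recruit eight primary schools (four experiment, four control").
- Statistical analyses: fixed effects for group, time and their interaction. "The school a student belongs to and the research site will be included as a random intercepts within the model", with a further random intercept for the student. There is no facilitator term and no random effect that varies with time above the student level.

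**The concern.** Where one person delivers the programme in two schools, that person's skill and adherence are common to both. The two schools are then not independent replications of the intervention, and the control arm has no matching correlation. The protocol gives some reason to expect facilitators to differ. It reports that, in the feasibility trial, the amount of detail on the cards was too much for some of them. It also leaves them to modify activities and to tailor the choice of activities, and it scores each one's adherence at Weeks 3 and 7.

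If such differences exist and the model leaves them out, the confidence interval for the intervention effect is too narrow. A facilitator with two or three schools also carries that many times the weight of a facilitator with one.

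**Working it through.** **The plan's own figure.** Design effect 1 + (25 − 1) × 0.20 = 5.8. Then 156 × 5.8 = 904.8, and 904.8 / 25 = 36.2, so 36 schools, 18 per arm, six intervention schools at each of three sites. The 156 is taken as given here.

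**The counts.** Six schools over four facilitators can only be split 2, 2, 1, 1 or 3, 1, 1, 1. At least one facilitator per site is shared, and 18 intervention schools have 12 facilitators. With the Abstract's four intervention schools per site, the split can be 1, 1, 1, 1 and nobody need be shared.

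**Assumption.** Total variance is 1. The facilitator variance f is not in the documents, so a range is shown. For equal school sizes, facilitators add f × 3 × Σload² / 18² to the variance of the intervention-arm mean. Σload² per site is 6 (one-to-one), 10 (2, 2, 1, 1) or 12 (3, 1, 1, 1). Error of a nominal 5% test is 2 × P(Z > 1.96 / √ratio), where ratio is true variance over the variance that the model assumes.

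**Check 1: comparison of post-test means, school clustering fully modelled.** Here f is part of the 0.20. Base variance is 2 × (0.20 + 0.80/25) / 18 = 0.0258. The extra from sharing is f × (3 × Σload² − 18) / 324.

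| f | 2, 2, 1, 1: ratio, error | 3, 1, 1, 1: ratio, error |
|---|---|---|
| 0.05 | 1.07, 5.8% | 1.11, 6.3% |
| 0.10 | 1.14, 6.7% | 1.22, 7.5% |
| 0.20 | 1.29, 8.4% | 1.43, 10.1% |

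The last row gives the facilitator the whole school ICC and is an upper limit.

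**Check 2: the group-by-time test that is planned.** Illustrative components, an assumption: student 0.5, school 0.2, residual 0.3. In each child's change from baseline the student, school and site intercepts cancel, which leaves 2 × 0.3 = 0.6. With 18 × 25 = 450 children per arm, the model's variance is 2 × 0.6 / 450 = 0.00267. A facilitator random intercept present at both times cancels in the same way: adding one with variance 0.1 leaves 0.00267 unchanged.

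Now let the facilitator effect arise only after baseline, as additional variance f, with loads 2, 2, 1, 1.

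- f = 0.01: extra 0.01 × 30/324 = 0.00093; ratio 0.00359 / 0.00267 = 1.35; error about 9%.
- f = 0.05: extra 0.05 × 30/324 = 0.00463; ratio 0.00730 / 0.00267 = 2.74; error about 24%.

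These treat the residual variance as known. The fitted residual would absorb a little of f, so they are slightly high.

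**How much is due to sharing.** With one-to-one matching (18/324 in place of 30/324) and the same model, the ratios are 0.00322 / 0.00267 = 1.21 and 0.00544 / 0.00267 = 2.04, with error about 7.5% and 17%. So a large part of the shortfall comes from having no school-by-time term. If the model had one that captured f at school level, ignoring sharing would still leave ratios of 0.00359 / 0.00322 = 1.11 and 0.00730 / 0.00544 = 1.34, with error about 6.3% and 9.0%.

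**The case against.** **Sharing is forced on only one version of the design.** This stands. A reader might infer that shared facilitators are a settled fact. The Abstract's count fits four facilitators exactly, so the point holds only on the 36-school figures. But the Abstract is no easy way out. Its 24 schools would put 904 / 24 = 37.7 children in each, a design effect of 1 + 36.7 × 0.20 = 8.3 and an effective sample of 904 / 8.3 = about 108, against the 156 required.

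**One-to-one delivery was never promised.** This also stands. Sharing does not in itself breach the plan. The gap is that the sample size and the model do not provide for it.

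**The facilitator variance is unknown, and delivery is standardised** by cards, common workshops, mentoring and observation. This is fair. In check 1, f of 0.01 to 0.02 with loads 2, 2, 1, 1 gives only 5.2% to 5.3%. Check 2 shows that the group-by-time test is more sensitive, because the school variance no longer dominates its standard error.

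**The 5.8% to 10.1% range might be read as the error rate of the planned analysis.** The documents do not support that. It belongs to a post-test comparison of means, and the plan specifies a group-by-time test.

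**A provider effect could be left to an analysis plan that is not shown.** Partly fair. But the article does list its random effects, and the point concerns what that list can and cannot capture. Adherence observation and attendance registers monitor delivery; they are not model terms.

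**Conclusion.** The point holds in conditional form. On the design that yields ~904 children, four facilitators per site cannot each serve a single school, and the stated random effects do not capture correlation between schools that share one. That the counts in the Abstract, Sample size calculation, Setting and participants, and Coach workshops sections do not fit one design is certain. It rests on reading four facilitators as four per site; four in total would make sharing heavier.

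The statistical consequence needs facilitators to differ in effect, and the documents give no value for that. If they do, the group-by-time standard error is too small. On the illustrative components, error is about 9% at f = 0.01 and 24% at f = 0.05, only part of it due to sharing. If f is close to zero, the harm is slight. The change is worth making because it is cheap and because the facilitator-to-school assignment has to be recorded while delivery is under way.

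**What to change.** 1. State the number of facilitators and of intervention schools per site consistently in the four sections named above.
2. Record which facilitator delivers in which school, and keep loads as even as possible (2, 2, 1, 1 in preference to 3, 1, 1, 1).
3. Let the cluster effects act on post-baseline change: a school-by-time random term, plus a facilitator-by-post-test random term in the intervention arm only. Alternatively, analyse change with schools sharing a facilitator as one cluster in the intervention arm and each control school as its own cluster. A facilitator random intercept alone should not be used for this purpose, since it leaves the group-by-time result unchanged.
4. Use a small-sample degrees-of-freedom correction.

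The cost is a change of wording, an assignment log and extra model terms, with no additional staff. The confidence interval will be wider. The facilitator variance will be poorly estimated: with loads 2, 2, 1, 1, six of the 12 facilitators have one school each and cannot be separated from it, so the estimate rests on six pairs of schools.

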### Fidelity of training

The fidelity of training of the coach delivering MOGBA will be measured through the coach’s adherence to a number of key determinants of successful MOGBA delivery, as agreed by the advisory panel. These determinants are listed below in Table 1, which is an adaption of a validated delivery protocol for physical education lessons [37].

**Table 1 pone.0253747.t001:** Fidelity of MOGBA coach training checklist.

Core Principles	OMG a TEST	Core Practices
**Clear game and Skill Introduction & Demonstration**	**O**rganise a group **M**ove students into the GO position for the activity **G**ive a demonstration and a few rules simultaneously (Get it Moving!)	Coach creates the game in an appropriate space, following equipment and health and safety guidelines Begin lessons with a clear statement of the lesson goals (SOL) Reviews prior skills and knowledge (movement focus from previous phases) before beginning instruction Provides direct and clear description of ‘How to Play’ Checks for understanding
**Targeted Elicitation**	**T**ry the game- resist over instruction, increase activity exposure **E**valuate the game and student performance Uses ‘**S**TOP’ to interject for development of activity or movement quality **T**ransitions students effectively between activities	Children perform the target SOL movements Coach checks for accurate performance and provides feedback Coach uses ‘change the game’ to ensure optimum engagement
**Repeated Guided Practice**		Coach provides repeated learning and practice opportunities Coach uses SER to differentiate activity Guides with cues (verbal, visual, physical) Provides individualised guided and varied practice opportunities Breaks down complex skills into smaller instructional units, where necessary
**Coach Responsiveness**		Provides individualized support and feedback Shows enthusiasm and is actively engaged with students Maintains class control Promotes high levels of reaching intended outcomes
**Movement assessment**		Coach identifies which children are to be assessed Accurately uses assessment criteria Affords repeated opportunities for assessment
**Child Engagement**		All children are actively participating, little wandering or off task behaviours Children are watching and listening when Coach is instructing Children are focusing their attention on the task and attempting the task as described by the teacher Children show enthusiasm for the activity tasks

### Fidelity of intervention

Each site lead will act as a mentor to the facilitators throughout the program, offering feedback that will be framed by the fidelity observational measure used in the training workshops (Table 1). This measure will also be used as a self-reporting mechanism for coaches to reflect upon their delivery after every session and will be used to form dialogue between the mentor and coach within the mentoring process. Mentoring ensures the coaches involved understand the format and purpose of the designed content, and for coaches to observe, undertake, problem solve and trouble shoot more effective practice with an academic partner, in the authentic context of their own coaching sessions [38–40].

Mentors will provide phone based feedback for the first 2 weeks of the program. All program facilitators will then be observed by their mentor at Weeks 3 and 7 of the 9-week intervention, with sessions referenced against content indicators, as established in Table 1, above. Sessions are also judged by adherence to (1) set-up criteria (2) play the game (3) change the challenge, and (4) assessment of movement, to obtain the percentage of agreement for each of these sets of statements (E.g. lesson agreement with one of four activity based statements = 25% activity agreement). These agreement values are used to indicate: i) if activity delivery at each time point was in line with a movement-based approach, and ii) if the fidelity of the instruction undertaken by the program facilitators was in line with the intended nature of the intervention. A register of attendance at learning sessions for facilitators and at activity sessions for children is maintained to monitor adherence at sessions across the intervention period.

The processes and procedures identified above represent the evaluation of the three big constructs of fidelity [41]: 1) *usability* (the extent to which the user can be trained to deliver MOGBA and is able to implement it), 2) *feasibility* (the extent to which MOGBA can be delivered in authentic settings of schools), and 3) *fidelity of implementation* (the extent to which MOGBA is delivered by end users in authentic contexts of school). In conducting these procedures we get at: 1) dose, 2) adherence, 3) exposure, 4) quality of delivery and 5) participant responsiveness, as well as addressing fidelity for the training of facilitators and the delivery of the intervention.

